### Statistical analysis

#### Student outcomes

At each follow-up time point the general linear model will test for the treatment factor, i.e. compare the intervention and control groups for each outcome measure. Corresponding baseline values of each outcome measure will be used as the covariate. In addition, possible effect of site will be examined by introducing a school factor in the analysis. Multi-level modeling will be used to compare the two groups in terms of the trend over time for each outcome. Both the last observation carried forward and multiple imputation techniques will be considered if missing data are substantial. Interim analysis will be conducted twice yearly, or upon request to facilitate the safety monitoring of the project.

Adherence will be measured using data automatically collected by the system (e.g. number of times each participant logs onto the site, amount of time spent on the site, proportion of activities completed).

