### Effect size and statistical power

The primary outcome of interest is changes in suicidal ideation from baseline measured at 10 and 22 weeks. This will be measured by the SIQ. No previous studies have tested the effects of an Internet-based CBT intervention on suicidal ideation, however one previous study [59] has reported moderate to large effect sizes in terms of reduced suicidal ideation, for face-to-face CBT among young people. If we assume that alpha is set at 0.05 and power at 0.80, then a sample size of 58 is required for each of the two groups (total n = 116) to detect a medium effect size. This is based on using the general linear model to compare the intervention and control groups with the baseline values of an outcome measure as the covariate. It is assumed (conservatively) that the covariate would explain 10% of the variance in the dependent variable. Using data from the pilot study, the intra-cluster correlation corresponding to the schools is estimated to be 0.023, which in turn gives an estimate of 1.1 for the design effect. So in order to take account of the clustering effect of the schools, the sample size needs to be inflated to 128 (116 × 1.1).

A previous RCT conducted by the study team with a similar population had a dropout rate of 24% [60]. The proposed study differs in that the intervention will be delivered by school staff and all follow-up assessments will be conducted at school. It will also employ a shorter follow-up period, however we have estimated a dropout rate of 24% meaning that we need to recruit 169 students (128/0.76) into the study. We estimate that we can recruit about 6 students from each school, so we need to recruit 28 schools. Based on data obtained from a pilot study conducted prior to developing the RCT [39] we consider these figures to be feasible.

Every effort will be made to promote participant retention, including close liaison with school staff, maximum flexibility on the part of research staff conducting follow-up assessments, and by employing a number of methods to contact students for follow-up assessments. These will include contacting the participant via the school wellbeing coordinator in the first instance, but also by contacting them directly via phone or email and contacting them via their parents/guardians if necessary.

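### The SIQ test that the trial is powered on is a separate model at each visit, so unless imputation uses the week-10 scores, the week-22 comparison ignores them for students lost afterwards

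*Protocol article*

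**What the plan says.** All references are to the protocol article.

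- Statistical analysis – Student outcomes gives the between-arm test: "At each follow-up time point the general linear model will test for the treatment factor". The adjustment is for baseline: "Corresponding baseline values of each outcome measure will be used as the covariate". A school factor is to be added to examine site effects.
- The same paragraph plans a longitudinal model with a different target: "Multi-level modeling will be used to compare the two groups in terms of the trend over time for each outcome".
- Missing data are handled conditionally: "Both the last observation carried forward and multiple imputation techniques will be considered if missing data are substantial".
- Effect size and statistical power names both follow-ups: "The primary outcome of interest is changes in suicidal ideation from baseline measured at 10 and 22 weeks". The power calculation uses the per-visit model: "This is based on using the general linear model to compare the intervention and control groups with the baseline values of an outcome measure".
- On losses, the same section says "we have estimated a dropout rate of 24" per cent. It does not split this by visit or by arm.

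The article does not say which of the two models is the main one. That the per-visit model has that role is inferred from the sample-size basis.

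**The concern.** A general linear model fitted at week 22 uses students with a week-22 SIQ. A student seen at week 10 and then lost contributes nothing to it unless the missing value is imputed, although the week-10 score is the most recent information on that student. The plan collects this score and already intends to fit a model that could use it, but directs that model at the trend rather than at the week-10 and week-22 differences.

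Two things are at stake. One is precision at week 22. The other is selective loss: if students leave after week 10 for reasons tied to their week-10 SIQ, and this link differs between arms, the students who remain are no longer comparable given baseline alone. A difference by arm is plausible here. Under Recruitment, withdrawal can follow from the clinical management of risk. School staff know the allocation and are the first route for follow-up contact. Intervention students have their ideation screen checked by staff at each module session. The article gives no direction for such loss.

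**Working it through.** **1. The plan's own figure.** Inputs from Effect size and statistical power: alpha 0.05, power 0.80, baseline explaining 10% of the variance, design effect 1.1, dropout 24%. Assumed: a two-sided test, and a medium effect of 0.5 SD, since no number is given.

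- Residual variance: 1 − 0.10 = 0.90.
- Normal approximation per arm: 2 × (1.960 + 0.842)² × 0.90 / 0.5² = 56.5, so 57. The exact t calculation gives a total of 116 (power 0.803), which is 58 per arm.
- 116 × 1.1 = 127.6, so 128. Then 128 / 0.76 = 168.4, so 169.

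The stated 116, 128 and 169 all reproduce.

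**2. Precision at week 22.** Let p10 be the proportion already missing at week 10, and ρ the correlation of the week-10 and week-22 scores given baseline. With students lost and not returning, and 76% observed at week 22:

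variance (joint model) / variance (separate model) = 1 − ρ² × (1 − 0.76 / (1 − p10)).

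The documents give neither quantity. Assumed: p10 = 12% (range 8–16%) and ρ = 0.6 (range 0.5–0.7). For the central case: 0.76 / 0.88 = 0.864, 1 − 0.864 = 0.136, and 1 − 0.36 × 0.136 = 0.951.

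| Missing at week 10 | ρ = 0.5 | ρ = 0.6 | ρ = 0.7 |
|---|---|---|---|
| 8% | 0.957 | 0.937 | 0.915 |
| 12% | 0.966 | 0.951 | 0.933 |
| 16% | 0.976 | 0.966 | 0.953 |

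The saving is about 5%, range 2–9%. At the planned effective size of 116, the noncentrality is (0.5 / √0.90) × √(116 / 4) = 2.838, giving power 0.803. With the variance multiplied by 0.951 it is 2.838 / √0.951 = 2.910, giving power 0.823.

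A wider set of assumptions (unadjusted correlation 0.4–0.8, and 25–100% of week-22 dropouts seen at week 10) gives ratios of 0.99 to 0.86. Students who miss both follow-ups add nothing under either model.

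**3. Bias at week 22.** Suppose loss after week 10 depends on the week-10 score. Among retained students in an arm, the mean week-22 residual given baseline is shifted by about ρ times the shift in their mean week-10 residual. The arm difference is biased by the difference between the two arms' shifts. If the arms share the same pattern, the shifts cancel.

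Simulation: 4000 trials per scenario, n = 169–170, true difference −0.50 SD, 12% lost at week 10, 24% lost by week 22, and log odds of loss 0.7 per SD of the week-10 SIQ. The selection strength and pattern are assumptions.

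| Loss pattern after week 10 | Bias, separate model (ρ = 0.5 / 0.6 / 0.7) |
|---|---|
| Same in both arms | about 0 (0.013 SD at most in any run) |
| High scorers lost, controls only | 0.042 / 0.050 / 0.060 SD |
| Controls lost when high, intervention lost when low | 0.076 / 0.096 / 0.109 SD |

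Repeat runs agreed to within 0.01 SD. The joint model's bias was at most about 0.004 SD in the two arm-dependent scenarios. As a share of the assumed 0.5 SD effect, 0.042 / 0.5 = 8% and 0.109 / 0.5 = 22%. The standard error of the estimate is about 0.17 SD.

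These two arm-dependent patterns shrink the effect. Losing high scorers from the intervention arm instead exaggerates it. With stronger selection (log odds 1.0 per SD, every dropout seen at week 10, unadjusted correlation 0.5–0.8) the separate model gave −0.585 to −0.642 for one-arm loss, a bias of 0.09–0.14 SD. It reached −0.792 in the extreme opposite-pattern case, a bias of 0.29 SD. Both size and sign depend on the scenario.

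**The case against.** The strongest reply is that the article states no complete-case rule. It names multiple imputation, which could condition on the week-10 score and would give the per-visit model much the same property as a joint model. Last observation carried forward would also bring the week-10 score into week 22, at the price of assuming no later change. A multi-level model is planned for every outcome, the coding of time is not given, and with visit as a factor it would yield both contrasts. Baseline-adjusted analysis at each visit is a standard and valid method. Details of imputation belong in an analysis plan that is not shown.

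Much of this stands. A reader might infer that the plan prescribes discarding these students; the text does not go that far. A reader might also infer that any link between the week-10 SIQ and later loss biases the week-22 test. That is too strong, because a pattern common to both arms leaves the difference about unbiased. The precision gain is modest, and under the assumed loss pattern it concerns week 22 only.

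What the reply does not remove is the allocation of tasks in the text. The test of the arms at each visit is given to the separate models, the multi-level model is given to the trend, and imputation is optional and not tied to the week-10 scores. The point is the choice of model for the two differences, not a missing imputation specification.

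**Conclusion.** The point holds as a better choice of main analysis, not as an error that invalidates the plan. Unless imputation using the week-10 scores is applied, the week-22 SIQ comparison leaves out information already collected on students lost after week 10.

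The certain cost is small: about 5% of the week-22 variance (2–9%), or power of about 0.82 instead of 0.80. It rests on the assumed split of dropout by visit and the assumed correlation. The possible cost is bias of roughly 0.04–0.11 SD in the milder illustrative scenarios, and only if loss depends on the week-10 SIQ differently by arm. The selection strength, its pattern, the correlation and the 0.5 SD reading of a medium effect are all assumptions. A reader might take these figures as a forecast that the week-22 result will be biased; the documents give no dropout pattern by arm and do not support that.

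The stated sample size is unaffected.

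**What to change.** In Statistical analysis – Student outcomes, make one repeated-measures (multi-level) model of the 10- and 22-week SIQ the main analysis.

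- Terms: arm, visit, arm-by-visit, baseline SIQ, baseline-by-visit and school. School belongs in the model because randomisation is stratified by it and the sample size allows for clustering within it.
- Covariance: unstructured within student.
- Data: every randomised student with at least one follow-up SIQ.
- Report: the adjusted arm differences at week 10 and week 22 from this model.
- Keep the per-visit general linear models as supporting analyses.

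The cost is analysis wording only. Multi-level modelling is already planned, and no new data or visits are needed. The downside is that the result relies on data being missing at random given the observed scores, and students with no follow-up score still contribute nothing.

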## Background

Suicide-related behaviours (SRB), including suicide attempts (SA) and suicidal ideation are common among young people. Up to 24% of 12–17 year-olds have reported suicidal ideation, and 7-11% have reported a 12-month prevalence of suicide attempt [1]. These behaviours are one of the greatest concerns for Australian young people [2] and are associated with a range of negative outcomes including completed suicide and premature mortality via other causes [3,4]. The prevention of suicide, and the development of a strategic research agenda targeting interventions for suicidal youth have both been cited as national priorities [5,6], yet there remains a lack of high quality intervention research for suicidal individuals [7], including youth [8].

Depression is the most common risk factor for SRB. Suicidal youth are six times more likely to have a psychiatric disorder than non-suicidal youth [9-11]. The most common disorder is depression, with between 60 and 80% of young people having a diagnosis of depression at the time of a SA [12]. Hopelessness has long been linked to increased suicide risk, including among young people, and is believed to mediate the relationship between depression and suicide-related behaviour [13,14].

Notwithstanding this, not all suicidal young people experience symptoms of depression; therefore interventions that specifically target suicidal young people are required. Good evidence exists regarding the treatment of youth depression [15], but there is limited knowledge regarding effective interventions for suicide-related behaviour [7,8]. Of the psychological approaches that have been tested Cognitive Behavioural Therapy (CBT) appears to be the most promising in terms of its ability to reduce suicidal ideation among adolescents and young adults, however further research is required [8].

CBT is used extensively in the treatment of adolescent depression [16] and is recommended as a first-line treatment for depressed youth [17]. Components frequently used with depressed adolescents include: basic psycho-education; pleasant activity scheduling; cognitive restructuring; problem-solving; and relaxation training [16].

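### Optional improvement, not an error: the SIQ model could also adjust for baseline depression and hopelessness, which are already collected in every student

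*Protocol article*

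**What the plan says.** Under Statistical analysis, Student outcomes, the protocol article compares the arms at each follow-up with a general linear model and fixes the adjustment: "Corresponding baseline values of each outcome measure will be used as the covariate". A school factor is to be introduced to examine site. No other prognostic covariate is named for the student outcomes.

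Effect size and statistical power uses the same single-covariate model and says of it: "It is assumed (conservatively) that the covariate would explain 10% of the variance in the dependent variable". On that basis, "a sample size of 58 is required for each of the two groups (total n = 116) to detect a medium effect size".

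The Background states "Depression is the most common risk factor for SRB" and "Hopelessness has long been linked to increased suicide risk, including among young people". Under Outcome measurements, the research assistant gives the listed measures at baseline, post-intervention and follow-up. They include the CDRS-R and RADS-2 for depression and the Beck Hopelessness Scale. Treatment history, substance use and help-seeking are collected separately as possible confounders; depression and hopelessness are not on that list.

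**The concern.** A baseline variable that predicts later SIQ, over and above baseline SIQ, lowers the residual variance and so the standard error of the arm difference. The plan links two measured variables to suicide risk and gives neither a place in the primary model.

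Two further features of the design bear on this. Randomisation is stratified by school only, so chance imbalance on depression or hopelessness can be dealt with only in the analysis. Planned dropout is 24%. If dropout depends on baseline depression or hopelessness, a model that conditions on them makes a missing-at-random assumption more plausible. At stake are a possible modest gain in precision and some protection against such dropout. The validity of the planned comparison is not at stake.

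**Working it through.** **Inputs from the protocol article (Effect size and statistical power)**
- "If we assume that alpha is set at 0.05 and power at 0.80". Sidedness is not stated; two-sided reproduces the plan's figure.
- Medium effect. No number is given; d = 0.5 is assumed and reproduces the plan's figure.
- R-squared of the baseline covariate: 0.10.
- Design effect: "the intra-cluster correlation corresponding to the schools is estimated to be 0.023, which in turn gives an estimate of 1.1 for the design effect".
- Dropout: "we have estimated a dropout rate of 24% meaning that we need to recruit 169 students (128/0.76) into the study".

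**Input not in the documents**
- The R-squared that baseline depression and hopelessness add once baseline SIQ is in the model. Assumed range: 0 to 0.10.

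**Step 1. Reproduce the plan's figure**

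Normal approximation: n per arm = 2(1.960 + 0.842)² × (1 − 0.10) / 0.5² = 56.5, so 57. The noncentral t version with one covariate (df = 2n − 3) gives 58, with power 0.803. Then 116 × 1.1 = 127.6, so 128, and 128 / 0.76 = 168.4, so 169. The plan's figures stand.

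The 58 per arm is also the right effective size for the comparison below, since 128 completers divided by the design effect of 1.1 give about 116.

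**Step 2. Add the two covariates**

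Noncentrality = d / √(1 − R²) × √(n/2), with n = 58, d = 0.5 and √29 = 5.385. The degrees of freedom are 116 − 2 − 3 = 111 with three covariates, against 113 with one. The ratio of standard errors to the planned model is √((1 − R²) / 0.90). The equivalent gain in sample size is 0.90 / (1 − R²).

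| Added R² | Total R² | Noncentrality | Power | SE ratio | Equivalent extra students |
|---|---|---|---|---|---|
| 0 | 0.10 | 2.838 | 0.803 | 1.000 | 0% |
| 0.02 | 0.12 | 2.870 | 0.812 | 0.989 | 2% |
| 0.05 | 0.15 | 2.920 | 0.825 | 0.972 | 6% |
| 0.10 | 0.20 | 3.010 | 0.847 | 0.943 | 12.5% |

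**Step 3. Cost if the covariates add nothing**

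Power goes from 0.8035 with one covariate to 0.8033 with three, a loss of about 0.0001.

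**Step 4. If baseline SIQ does better than the conservative 10%**

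With R² = 0.25 from baseline SIQ alone, power is already 0.869; adding 0.02 or 0.05 gives 0.878 or 0.891. With R² = 0.36 it is 0.916, then 0.924 or 0.935. Power is higher to start with, and the extra covariates move it less.

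**The case against.** The strongest case against is that nothing here is wrong. Adjusting for the baseline value of the outcome is a standard, valid analysis. It matches the model behind the sample size, and the planned power does not depend on any further covariate. Further covariates may also sit in an analysis plan that is not shown. All of this stands, and it is why the point is only a suggestion. It remains worth making because the article states the covariate rule positively, and the suggestion changes that rule.

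A reader might infer three stronger things that the documents do not support.

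- **That baseline SIQ is expected to be a weak covariate.** The 10% is labelled a conservative assumption for the sample size. It is a cautious input and forecasts nothing about the variance left unexplained.
- **That the model contains baseline SIQ and nothing else.** The same section introduces a school factor.
- **That precision is demonstrably being lost on the leading risk factors.** The Background calls depression the most common risk factor for suicide-related behaviour and describes hopelessness as linked to suicide risk; it does not rank the two together at the top. Neither statement shows that these scores predict follow-up SIQ once baseline SIQ is known, in a sample where every student has recent ideation.

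The documents give reasons to expect a small increment. The CDRS-R itself rates suicidal ideation, so it overlaps with baseline SIQ. Hopelessness is said to mediate the link between depression and suicide-related behaviour, so the two scores overlap with each other.

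Two lesser objections also have force. Chance imbalance does not bias a randomised comparison. Baseline scores could also be used in the multiple imputation that the plan says it will consider. That use is conditional on missing data being substantial, however, whereas a covariate in the model acts in any case.

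**Conclusion.** The planned SIQ analysis is sound and the sample size reproduces. What holds is a nearly free improvement: two baseline scores that the plan itself connects to suicide risk are available in every student and have no stated role in the primary model. Using them would raise power from 0.803 to between 0.803 and 0.847, and lower the standard error by 0% to 6%, if they add 0 to 0.10 to R-squared. That range is an assumption, and the lower part of it is the more plausible given the overlap of the measures. The figures also rest on d = 0.5, a two-sided test and 58 per arm as the effective size. The benefit under dropout is qualitative and cannot be sized from the documents.

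**What to change.** In Statistical analysis, Student outcomes, add one sentence, fixed before any comparison of the arms: the general linear model for SIQ at 10 and 22 weeks contains arm, baseline SIQ, one baseline depression score (for example the CDRS-R total) and the baseline Beck Hopelessness total, with the school term as planned. Keep the model adjusted for baseline SIQ without these two scores as a sensitivity analysis.

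The documents do not settle which depression scale to use. What matters is that one is named in advance.

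The cost is two degrees of freedom and a simple stated rule for missing baseline totals. No new data are needed, and the sample size need not change.

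### Last observation carried forward is left open as a method for the SIQ with 24% dropout expected; it would bias the treatment difference and should be removed as a candidate

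*Protocol article*

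**What the plan says.** Under Statistical analysis, Student outcomes, the protocol article plans a general linear model at each follow-up, with the baseline value as covariate. For the longitudinal comparison it adds: "Multi-level modeling will be used to compare the two groups in terms of the trend over time for each outcome". On missing data it says: "Both the last observation carried forward and multiple imputation techniques will be considered if missing data are substantial". It does not define substantial and does not rank the two methods.

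Under Effect size and statistical power it expects a sizeable loss: "we have estimated a dropout rate of 24% meaning that we need to recruit 169 students (128/0.76) into the study". The 24% comes from an earlier trial by the same team in a similar population. It is not split by arm or by visit. The primary outcome is change in SIQ at 10 and 22 weeks.

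Entry requires any level of suicidal ideation in the past month, in students who present to school wellbeing staff. The Background reports that ideation fell over the program in the uncontrolled pilot of 21 students, without giving the size of the fall.

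**The concern.** At 24% loss, about 0.24 × 170 = 41 of the 170 students would lack an SIQ endpoint, so the missing-data method matters for the main result. The document's own evidence suggests that scores will fall after entry. LOCF then substitutes a value that is systematically wrong and treats it as observed. For a student lost before week 10 the substituted value is the baseline score. For a student seen at week 10 and lost by week 22, the week-22 value becomes the week-10 score.

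At stake is the primary treatment difference. It is diluted if both arms lose students equally, and distorted in either direction if they do not. Unequal loss is plausible, since one arm is asked to complete eight supervised modules with homework and the other receives usual care. Leaving the choice between two methods that can give different answers until the data are in also exposes the primary result to a charge of selection.

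**Working it through.** **1. The plan's own figure.**
- The stated settings are alpha 0.05 and power 0.80, giving 58 students per arm. The target is put as "total n = 116) to detect a medium effect size", and the baseline adjustment supposes that "the covariate would explain 10% of the variance in the dependent variable".
- Taking medium as 0.5 SD (the number is not printed) and a two-sided test, the residual SD is √0.9. A noncentral-t calculation for the baseline-adjusted model gives power 0.7965 at 57 per group and 0.8035 at 58. The 58 is reproduced.
- For clustering: "the intra-cluster correlation corresponding to the schools is estimated to be 0.023, which in turn gives an estimate of 1.1 for the design effect". With about 6 students per school, 1 + 5 × 0.023 = 1.115, printed as 1.1. Then 116 × 1.1 = 127.6, rounded to 128, and 128 / 0.76 = 168.4, rounded to 169.
- The sample size rests on completers and does not depend on LOCF.

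**2. Expected LOCF difference at week 10.** Let c be the control-arm improvement in SD, δ the true extra improvement in the Reframe-IT arm, and d_T and d_C the loss before week 10 in the Reframe-IT and control arms, at random within arm. Then

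LOCF difference = (1 − d_T)(c + δ) − (1 − d_C)c.

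The documents give neither c nor the loss by arm, so both are assumptions shown over a range. δ = 0.50 except under the null.
- Equal loss of 24%: 0.76 × 0.50 = **0.38 SD**, whatever c is.
- 33% Reframe-IT, 15% control, c = 0: 0.67 × 0.50 = 0.335, or **0.33 SD** in simulation.
- Same split, c = 0.5: 0.67 × 1.0 − 0.85 × 0.5 = 0.245, or about **0.24 SD**.
- No true effect, same split, c = 0.8: 0.67 × 0.8 − 0.85 × 0.8 = **−0.144 SD**, an apparent harm. Reversing the split gives +0.144 SD, an apparent benefit.
- No true effect, 28% Reframe-IT, 20% control, c = 0.8: 0.72 × 0.8 − 0.80 × 0.8 = **−0.064 SD**.

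**3. Power and type I error.** These come from simulation with 85 per arm, baseline correlation √0.10 = 0.316, baseline-adjusted linear model, 4,000 runs per setting, all loss before week 10 and clustering ignored.

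| Setting | LOCF estimate | LOCF rejection rate | Observed data |
|---|---|---|---|
| 24%/24%, δ = 0.5, c = 0 | 0.38 | about 80% | 0.50, 83-84% |
| 24%/24%, δ = 0.5, c = 0.5 | 0.38 | about 74% | 0.50, 83-84% |
| 24%/24%, δ = 0.5, c = 0.8 | 0.38 | about 70% | 0.50, 83-84% |
| 24%/24%, no effect | 0 | about 5% | about 5% |
| 33%/15%, δ = 0.5, c = 0 | 0.33 | about 67% | 0.50, 83% |
| 33%/15%, δ = 0.5, c = 0.5 | 0.24 | about 38% | 0.50, 83% |
| 33%/15%, no effect, c = 0.8 | −0.14 | about 17% | about 5% |
| 28%/20%, no effect, c = 0.8 | −0.06 | about 7% | about 5% |

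Loss is given as Reframe-IT/control; a positive estimate favours Reframe-IT. Repeat runs differ by one or two percentage points. Observed-data power exceeds 80% because 85 × 0.76 = 64.6 completers per arm are expected against the 58 required, and the simulation does not spend the clustering allowance. Loss is random within arm, so the observed-data analysis is unbiased here by construction.

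**The case against.** The strongest reply is that LOCF is not the plan. It is to be considered, only if missing data are substantial, and alongside a defensible alternative. The analysis to which the article does commit, the baseline-adjusted linear model, is unbiased on observed data in the simulation above and exceeds its power target. The final choice of method and the threshold for substantial could properly sit in an analysis plan that is not shown. This stands as far as it goes: the absence of a threshold is not itself the defect. What remains is that the article names, on equal footing with multiple imputation, a method that gives a worse answer.

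Four stronger readings are tempting and are not supported:
- **That LOCF would carry crisis-level scores forward.** The article admits any level of ideation and sets no SIQ cut-off. The bias needs only that scores change after baseline.
- **That LOCF would manufacture a benefit.** With equal loss, type I error is kept. With more loss in the Reframe-IT arm the false signal is towards harm. A false benefit needs more loss among controls together with improvement in that arm.
- **That the larger errors are to be expected.** The power of 38% requires a control improvement of 0.5 SD; with none it is 67%. A baseline correlation of 0.6 would raise the 17% to about 22%, but the article's own 10% of variance implies 0.316. At c = 0.4 the 17% falls to about 8%.
- **That all dropouts keep their baseline score.** Students seen at week 10 and lost later carry the week-10 score, so loss entirely before week 10 is the unfavourable case. The article also hopes to retain students better through assessment at school and a shorter follow-up.

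**Conclusion.** The point holds in a limited form. The article leaves open, for the primary outcome, a method that biases the SIQ difference whenever scores change after baseline, and it expects enough dropout for this to matter.

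The firmest figure is the equal-loss case. A 0.50 SD effect becomes 0.38 SD, a loss of 24%, and power falls from 83-84% to between 80% and 70%, with type I error intact. This rests on an effect of 0.5 SD, loss at random within arm, and all loss before week 10. The unequal-loss results also depend on an assumed split and an assumed common improvement. They range from a type I error of about 7% at 28%/20% to about 17% at 33%/15%, and show that the direction of bias cannot be known in advance. The plan should be changed before unblinding, but the design and sample size are not called into question.

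**What to change.** Remove LOCF as a candidate. Name the multi-level model that the article already plans as the primary SIQ analysis, fitted to all available scores with time as a category, treatment-by-time interaction, baseline SIQ and a school effect. It is valid under missing at random without imputation, and it uses the week-10 score of a student missing at week 22. A student with no post-baseline score adds little to it, so the missing-at-random assumption needs testing. Do this with multiple imputation as sensitivity analysis, including versions in which imputed scores are shifted by a stated delta.

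The cost is a change of wording in the analysis section and slightly more analysis work. Sample size, visits and trial conduct are unchanged.
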